### Safety assessment

Participants will be asked to report any adverse events or related information during the treatment phase and the follow-up phase. The details of every adverse event will be reported in the Case Report Form.

### Data management

The Independent Data Monitoring Committee (IDMC) is a group of clinicians and biostatisticians appointed by study sponsors who provide independent assessment of the safety, scientific validity, and integrity of clinical trials [21]. The IDMC members of this study include two clinicians and one biostatistician with expertise in clinical trial and interim data analysis. The functions and frequency of its meetings are dictated by the DMC charter. The IDMC can recommend premature closure or reporting of the trial.

In order to improve patient compliance, we have taken the following measures: (1) we explain the purpose, significance, and related follow-up time of the study before enrollment; (2) we perform regular telephone follow-up to be informed of the changes in the subject’s condition and provide necessary assistance.

Jiangsu Famous Medical Technology Co., Ltd. in Nanjing, China is responsible for managing the data (e.g., plans for data entry, coding, security, and storage, double data entry; range checks for data values), formulating statistical analysis plans, writing statistical analysis reports, and final review by the project responsible unit.

### Statistical analysis

All data will be analyzed according to the intention-to-treat (ITT) and per-protocol (PP) analyses to reduce deviation. The modified intention-to-treat (mITT) analysis set is a subset of the ITT population and allows the exclusion of some randomized subjects in a justified way. The PP analysis set will include patients who fully complete the trial. The mITT analysis set is used for efficacy and the PP analysis set for safety. Continuous variables will be presented as mean and standard deviation or median and interquartile range according to the Kolmogorov-Smirnov test, and categorical variables as number of patients and proportion.

The Student’s *t* test will be used to compare differences in measurement data. The rank sum test will be used to deal with ranked data, the chi-squared test will be used to analyze categorical data, and the repeated measures analysis of variance (ANOVA) test will be used to analyze multiple measurements at different time-point data. If the effect of the different centers is significant, the Cochran-Mantel-Haenszel (CMH) chi-square test or analysis of covariance (ANCOVA) test is used to correct it. A statistician not involved in data collection will conduct all statistical analyses using SPSS version 23.0 software (SPSS Inc., Chicago, IL, USA).

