## Methods/design

### Objectives

The study objectives are as follows:
Clinical outcome: to test the clinical efficacy of CM for patients with AECOPDSafety evaluation: to evaluate the safety of CM on AECOPD patients.

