### Randomization and blinding

A central dynamic stochastic distribution method is adopted. The randomization sequence will be generated by the ‘proc plan’ procedure of SAS software (version 23.0) according to stratified block randomization with a block size of 6, and the random number and group assignment will be obtained from a central randomization system provided by Jiangsu Famous Medical Technology Co., Ltd. in Nanjing, China. Eligible AECOPD patients will be randomly divided into an experimental group and a control group in a 1:1 allocation ratio. The data management and statistical analysis units formulate a random distribution scheme according to the test scheme. They then implement and manage the random distribution scheme through a central random distribution interactive voice operating system. The researcher obtains the subject assignment code via the Internet or phone.

All participants, trial participants, care providers, and outcome assessors except for the data analysts are blind to treatment allocation. The CM placebo packaging in the control group is consistent with the CM granules, and the odor and color are also similar to those of the experimental group CM granules, but there is no clinical effect. If serious adverse events that threaten the safety of participants occur, we will immediately stop the intervention, cancel the blinding, and contact the Institutional Review Board.

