### Withdrawal, dropout, and discontinuation

Participants can refuse to participate in the study and follow-up evaluation after enrollment. Other indications for withdrawal are the following situations: (1) development of serious disease (such as acute respiratory failure, acute myocardial infarction, acute heart failure, or stroke) during the observation period; (2) receiving other CM for AECOPD during the observation period; (3) participants who present with serious adverse events (such as death, disability, surgery, or congenital malformations) (4) participants who refuse to continue to participate in the RCT; (5) those lost to follow-up.

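### Safety is assigned to a completers-only per-protocol set, so the safety analysis omits deaths and, on the plain reading, most or all other serious adverse events

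*Protocol article*

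**What the plan says.** Safety is one of the two objectives of the trial: "to evaluate the safety of CM on AECOPD patients" (Objectives). Adverse events are collected broadly: "Participants will be asked to report any adverse events or related information during the treatment phase and the follow-up phase" (Safety assessment), with details entered in the Case Report Form.

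The analysis population is then narrowed in the Statistical analysis section. The assignment is "The mITT analysis set is used for efficacy and the PP analysis set for safety", and the set is defined by "The PP analysis set will include patients who fully complete the trial". The section opens with a more general sentence: "All data will be analyzed according to the intention-to-treat (ITT) and per-protocol (PP) analyses to reduce deviation". The article names no safety set of all treated or all randomised patients.

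The section Withdrawal, dropout, and discontinuation gives as indications for withdrawal, among others, "development of serious disease (such as acute respiratory failure, acute myocardial infarction, acute heart failure, or stroke) during the observation period" and "participants who present with serious adverse events (such as death, disability, surgery, or congenital malformations". The Randomization and blinding section adds that when a serious adverse event threatens a participant's safety, "we will immediately stop the intervention, cancel the blinding, and contact the Institutional Review Board".

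**The concern.** The patients most likely to have been harmed are those who die, are withdrawn or stop early. A safety set restricted to completers is selected on the outcome it is meant to measure. If the granules caused serious events that lead to withdrawal, those events would leave the safety comparison along with the patients. The arms could then look alike in completers although they differ in everyone treated. Non-serious events would be affected too, to the extent that patients who have them do not complete.

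At stake is the validity of the comparative answer to a stated objective. The choice of set is printed in the article, so it is not a detail left to an analysis plan that is not shown.

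**Working it through.** **Step 1. The rule, side by side.**

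| Element | Source (protocol article) | Consequence |
|---|---|---|
| Safety is analysed in the PP set | Statistical analysis | Only PP members count |
| The PP set consists of completers | Statistical analysis | A patient who dies cannot be a member |
| Serious adverse events and serious disease are indications for withdrawal | Withdrawal, dropout, and discontinuation | A withdrawn patient is, on the plain reading, not a completer |
| Adverse events are asked for in both phases | Safety assessment | The events are collected, then left out for non-completers |

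For deaths the exclusion is certain. For other serious events it depends on how consistently the indication leads to withdrawal, and on whether withdrawal means leaving treatment or leaving the study. The text settles neither.

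**Step 2. The plan's own figure.** The inputs in the Sample size section are z-values 1.96 and 1.28, a difference of 2 points, and standard deviations 5.50 and 5.87 (the previous study's placebo value; the formula inputs print 5.78).

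- n = (1.96 + 1.28)² × (5.50² + 5.87²) / 2² = 10.4976 × 64.7069 / 4 = 169.8, rounded up to 170 per group.
- 170 / 0.9 = 188.9, rounded up to 189 per group; 2 × 189 = 378.
- With 5.78 the formula gives 167.1, rounded up to 168. The difference has no bearing on this point.

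**Step 3. How many patients leave the safety analysis.** At the planned 10% dropout, 378 × 0.10 = 37.8, about 38 patients. That leaves 378 − 38 = 340. This is the only size that follows from the plan itself.

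**Step 4. Illustrations. All event rates here are assumptions.**

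*Serious events.* Let p be the proportion of an arm with a non-fatal serious event and w the share of those patients who are withdrawn. The expected number left in the safety set is 189 × p × (1 − w). The plain reading is w = 1.

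| Assumed p, arm A vs arm B | Expected patients among all randomised | In the PP set if w = 1 |
|---|---|---|
| 2% vs 5% | 189 × 0.02 = 3.8 vs 189 × 0.05 = 9.5 | 0 vs 0 |
| 5% vs 10% | 189 × 0.05 = 9.5 vs 189 × 0.10 = 18.9 | 0 vs 0 |

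If w is below 1, some events remain, but those remaining are a selected subset.

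*Deaths.* For mortality of 1% to 4.3%, 378 × 0.01 = 3.8 and 378 × 0.043 = 16.3, so about 4 to 16 deaths fall outside the safety set. The 4.3% is the US in-hospital figure for 2006 cited in the Background and serves only as a scale. The 1% has no source in the article.

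*Any adverse event.* If 10% of completers and 50% of non-completers had an event, the rate in everyone would be 0.9 × 10% + 0.1 × 50% = 14%, while the PP set would show 10%.

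**The case against.** The strongest reply is that deaths do not disappear from the trial. Mortality and intubation are secondary outcomes, scheduled in Table 1 from Day 4 to Day 42, and death also counts as treatment failure at Day 14. These would presumably be analysed in the modified intention-to-treat set. This stands. A reader might infer that the trial would report almost no deaths, and the documents do not support that: the omission concerns the safety analysis. The reply does not extend to myocardial infarction, stroke, disability or surgery, which have no outcome of their own.

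Second, the section's opening sentence, read literally, gives all data an intention-to-treat analysis as well. The later sentence is specific to safety and more naturally governs. At best the section contradicts itself on the safety population, which still needs correcting.

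Third, it is tempting to say that the number of serious events in the safety set is zero by construction, or that everyone who stops for a non-serious event is excluded. Neither is established. The article lists indications for withdrawal and does not make withdrawal automatic. Non-serious events are not on that list, so such patients are lost only if they refuse to continue, are lost to follow-up, or if completion includes finishing the granules. Non-serious events in completers are still counted.

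Fourth, harms are not invisible: they go into the Case Report Form, an independent monitoring committee assesses safety, and threatening serious events trigger unblinding and contact with the review board. These are safeguards during conduct. They do not repair the final comparison between arms.

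Fifth, the 4.3% mortality may not carry over. The trial also screens outpatients and excludes patients with NYHA Class IV heart failure, unstable haemodynamics or a need for invasive ventilation. That is a fair limit on the illustration and leaves the rule itself untouched.

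**Conclusion.** The point holds, and the text is wrong as written. The safety analysis excludes all deaths with certainty, most or all other serious adverse events on the plain reading of the withdrawal section, and the adverse events of the remaining non-completers. The group left out is about 38 of 378 patients if dropout is as planned. The bias in any event rate cannot be sized from the article. The figures in the working show only how large it could be under assumed rates, and none of them is an estimate for this trial.

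The conclusion rests on two readings: that the specific sentence on safety prevails over the general opening sentence, and that a withdrawn patient has not completed the trial. Because safety is a stated objective, this should be corrected before the analysis.

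**What to change.** Replace the safety half of the sentence with: *safety is analysed in all randomised patients who took at least one dose of granules, grouped by treatment actually received, counting all recorded adverse events and deaths up to Day 42 whether or not the patient completed the trial.*

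Reconcile the opening sentence of the section with this, for example by confining it to efficacy data, so that only one safety population is stated.

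The cost is a text change and a small amount of analysis work. The sample size stays at 378, and no treatment or withdrawal rule has to change. The article reports recruitment as complete, but an analysis-set rule can still be corrected before the analysis. Events already in the Case Report Form need no new data. The article does not say that adverse-event collection continued after withdrawal, and withdrawals include patients lost to follow-up. The sponsor should therefore confirm where follow-up continued and report, by arm, where it did not.

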### Sample size

The COPD Assessment Test (CAT) will be used as the main outcome. According to previous study results, the average CAT score of AECOPD patients treated by CM is 16.54 ± 5.50 and that of the placebo is 18.33 ± 5.87 [8]. The most reliable estimate of the minimum important difference of the CAT is 2 points [9]. Assuming that α is 0.05 and power is 90%, the two-sided *Z*
_1-α/2_ is 1.96 and *Z*
_1-_β is 1.28. The standard deviation of the first group (σ_1_) is 5.50 and that of the second group (σ_2_) is 5.78, and the clinically meaningful difference (δ) is 2. Based on the formula $$ n=\frac{{\left({{Z_{1-}}_{\alpha}}_{/2}+{Z_{1-}}_{\beta}\right)}^2\times \left({\sigma_1}^2+{\sigma_2}^2\right)}{\delta^2} $$, the sample size in each group is 170. Considering a 10% dropout rate over the course of the study, 189 patients will be enrolled in each group. The total sample size will be 378.

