### Outcomes

#### Primary outcome: COPD Assessment Test (CAT)

The primary outcome of this study will be changes in the CAT between baseline, 14 days after treatment, and the 28 and 42 days follow-ups. We will use the CAT to evaluate the impact of AECOPD on a person’s life and how this changes over time.

The CAT is an 8-item questionnaire designed to assess and quantify health-related quality of life and symptom burden in patients with COPD [10, 11]. Each questionnaire item is presented as a semantic 6-point (0–5) differential scale, providing a total score out of 40. Scores of 0–10, 11–20, 21–30, 31–40 represent mild, moderate, severe, or very severe clinical impact, respectively [12]. Evidence has shown the CAT may also prove useful in clinical trials to objectively assess the ability of novel interventions to reduce AECOPD severity [13], and it is a potentially useful instrument to assess the efficacy of treatments following COPD exacerbations [14].

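### Unless missing values are imputed first, the repeated measures ANOVA named for CAT and the other serial scales turns the mITT efficacy analysis into something close to a completer analysis; a mixed model would use the partial data

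*Protocol article*

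**What the plan says.** The Statistical analysis section begins "All data will be analyzed according to the intention-to-treat (ITT", paired with a per-protocol analysis. It then assigns efficacy to an mITT set, from which some randomised patients may be left out with justification, and limits the per-protocol set to patients who finish the trial. For serial data it states that "the repeated measures analysis of variance (ANOVA) test will be used to analyze multiple measurements at different time-point data". The software is SPSS 23.0. Student's t test is named for measurement data, the rank sum test for ranked data, and ANCOVA or CMH if centre effects are significant.

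The primary outcome is "changes in the CAT between baseline, 14 days after treatment, and the 28 and 42 days follow-ups". Table 1 shows four visits for CAT, SF-36 and COPD-PRO (Days 0, 14, 28, 42) and seven for mMRC (Days 0, 4, 7, 10, 14, 28, 42).

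The section on withdrawal, dropout and discontinuation lists, among its reasons, "development of serious disease (such as acute respiratory failure, acute myocardial infarction, acute heart failure, or stroke) during the observation period", together with serious adverse events (including death), use of other Chinese medicine for the exacerbation, refusal and loss to follow-up. The Participants section also allows rejection of patients whose data are too sparse to judge. The Sample size section allows for 10% dropout. No imputation rule is given; the Data management section assigns the writing of a statistical analysis plan to a separate unit.

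**The concern.** Classical repeated measures ANOVA, as usually run in SPSS, needs a full set of visits for each patient. In that analysis, a patient with a valid Day 14 CAT who misses only Day 42 contributes nothing, not even the Day 14 value.

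Two things are at stake.

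- **Validity.** The reasons for withdrawal include clinical deterioration of the kind CAT is meant to reflect. If such withdrawals differ between arms, the completers are no longer a randomised comparison. The mITT and per-protocol results would also rest on nearly the same patients, so their agreement would give little reassurance.
- **Precision.** Values already collected from partly followed patients are discarded. The loss grows with the number of visits, so mMRC is more exposed than CAT if it is analysed this way.

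**Working it through.** **Inputs from the Sample size section.** "Assuming that α is 0.05 and power is 90%, the two-sided" normal quantiles are 1.96 and 1.28; "the clinically meaningful difference (δ) is 2"; dropout is 10%; 189 patients are enrolled per group. Two values of the second SD are printed: "the average CAT score of AECOPD patients treated by CM is 16.54 ± 5.50 and that of the placebo is 18.33 ± 5.87", and then "The standard deviation of the first group (σ_1_) is 5.50 and that of the second group (σ_2_) is 5.78".

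**Step 1: reproduce the plan's figure.** n = (1.96 + 1.28)² × (σ₁² + σ₂²) / δ².

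- With 5.50 and 5.87: 10.4976 × (30.25 + 34.4569) / 4 = 169.8, so 170.
- With 5.50 and 5.78: 10.4976 × (30.25 + 33.4084) / 4 = 167.1, so 168.

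The stated 170 follows from 5.87, and 5.78 looks like transposed digits. Then 170 / 0.9 = 188.9, so 189 per group and 378 in total. The stated size is reproduced, and 5.87 is used below.

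**Step 2: power by share of patients with an incomplete CAT series.** Power = Φ(δ / √((σ₁² + σ₂²)/n) − 1.96), where n = 189 × (1 − share incomplete). This is a single-visit comparison, as in the plan's own formula.

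| Incomplete | n per group | Power |
|---|---|---|
| 0% | 189 | 92.8% |
| 10% | 170.1 | 90.0% |
| 15% | 160.7 | 88.3% |
| 20% | 151.2 | 86.4% |
| 30% | 132.3 | 81.6% |

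For example, at 20%: √(64.7069/151.2) = 0.654; 2/0.654 = 3.057; 3.057 − 1.96 = 1.097; Φ(1.097) = 0.864.

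The plan's allowance covers the loss up to 10%. Every row above 10% is an assumption, because the article gives no rate of missed visits.

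**Step 3: what missed-visit rate would use up the allowance?** Assume a missing rate p per post-baseline visit, independent across visits, so the complete share is (1 − p)^k.

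- CAT, k = 3: 2% per visit leaves 94.1% complete (power 91.3%), 5% leaves 85.7% (88.6%) and 10% leaves 72.9% (83.1%). Setting (1 − p)³ = 0.90 gives p ≈ 3.5%.
- mMRC, k = 6: the same rates leave 88.6%, 73.5% and 53.1% complete. Setting (1 − p)⁶ = 0.90 gives p ≈ 1.7%.

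Independence is a simplification. If missed visits cluster in the same patients, fewer series are broken.

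**Step 4: direction and possible size of bias, by illustration only.** Suppose deleted patients score g CAT points worse than the rest, and 10% of control and 5% of CM patients are deleted. The completer difference is then 2 − (0.10 − 0.05) × g. With g = 5 it is 1.75; with g = 8 it is 1.6. If deletions were commoner on CM, the sign would reverse and the benefit would be overstated. None of these rates or gaps comes from the article.

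**The case against.** The strongest reply is that list-wise deletion is not built into the plan. ANOVA on imputed data keeps every patient, and the imputation rule is an item a protocol article normally leaves to the statistical analysis plan, which is not shown. That stands, and it limits the point in several ways.

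- A reader might infer that the analysis cannot be an ITT analysis. The documents do not support this: imputation could precede the ANOVA, and efficacy is assigned to mITT, which already permits justified exclusions.
- A reader might infer that a patient missing only Day 42 is lost from the primary analysis. That is not established either. The same section names a t test, the sample size rests on a two-sample comparison, and no sentence says which test is primary for CAT. A Day 14 t test would keep that patient. The four-visit definition of the outcome does, however, place CAT under the sentence on serial data.
- A reader might infer that 90% power is forfeited. It is not, unless more than 10% of patients have an incomplete series.
- mMRC might go to the rank sum test as ranked data, in which case its retention figures do not apply.
- The usual remedy does not reach everyone. The first post-baseline CAT is at Day 14, so a patient who dies or withdraws earlier has no response value for a mixed model either.

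What survives is that the article names a specific method, and a better one exists for the same data. The objection to the method does not depend on a missing-data rule being absent, although the size of the harm does.

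**Conclusion.** The point holds in conditional form. If missing values are not imputed first, the named ANOVA reduces the mITT analysis of the serial scales to nearly a completer analysis. Given the listed withdrawal reasons, the loss may be related to outcome. It is uncertain how much deterioration leads to missing CAT values, because the article does not say whether withdrawn patients are still assessed.

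For CAT, power remains about 90% with up to 10% incomplete series, and is about 86% at 20% and 82% at 30%. These figures rest on a single-visit comparison, a 2-point difference, SDs of 5.50 and 5.87, and assumed rates of incompleteness; averaging over visits would change them. The possible bias cannot be sized from the article. The case for change is that a mixed model uses data already collected at almost no cost, not that a failure has been shown.

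**What to change.** Replace repeated measures ANOVA with a likelihood-based mixed model for repeated measures on all observed post-baseline values of randomised patients. Include treatment, visit, treatment-by-visit interaction, centre and baseline score as covariate, with unstructured within-patient covariance. Report the adjusted treatment difference at one pre-specified primary visit. Which visit that should be is a separate decision for the sponsor. Use the same model for SF-36 and COPD-PRO, and for mMRC if it is not treated as ranked data.

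Add a sensitivity analysis covering patients with no post-baseline CAT, such as those who die or withdraw before Day 14, and departures from missing at random. If the ANOVA is kept instead, state the imputation rule that precedes it.

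The cost is analysis wording and a standard mixed-model procedure, which SPSS provides; no new data, visits or patients are needed. The downside is reliance on the missing-at-random assumption. Because the blinding section exempts data analysts, the choice should be documented before outcome data are examined by arm.

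### The plan neither keeps the Day 0 score out of the repeated measures ANOVA nor uses it as a covariate; if Day 0 is a time level and the group main effect is reported, a 2-point CAT difference shrinks to 1.5

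*Protocol article*

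**What the plan says.** The Statistical analysis section of the protocol article assigns Student's t test to continuous data. For outcomes measured more than once it says that "the repeated measures analysis of variance (ANOVA) test will be used to analyze multiple measurements at different time-point data". It lists no levels for the time factor and does not say which term of the model is the test of efficacy. ANCOVA appears in the same paragraph, but only as a correction if the centre effect is significant; baseline CAT is not named as a covariate.

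The Outcomes section defines the primary outcome as "changes in the CAT between baseline, 14 days after treatment, and the 28 and 42 days follow-ups". Table 1 schedules CAT, SF-36 and COPD-PRO at Days 0, 14, 28 and 42.

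The Sample size section plans a single two-group comparison of mean CAT in which "the clinically meaningful difference (δ) is 2".

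**The concern.** Table 1 and the outcome definition set Day 0 beside the three later CAT assessments, so a natural reading of the ANOVA sentence puts all four into the time factor. The group main effect of such a model is the average of the four visit differences. Randomisation makes the expected Day 0 difference zero, so that average is pulled towards zero and also picks up any chance imbalance at baseline. A true post-treatment benefit equal to the minimum important difference would then be reported below it, and under moderate or high correlation between visits the test would fall short of the planned power.

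A further cost does not depend on that reading: the text gives the Day 0 score no covariate role, although it is collected for every patient and adjusting for it would sharpen the comparison.

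**Working it through.** **Inputs.** From the Sample size section: "Assuming that α is 0.05 and power is 90%, the two-sided" normal quantiles are 1.96 and 1.28; δ = 2; "the average CAT score of AECOPD patients treated by CM is 16.54 ± 5.50" and "that of the placebo is 18.33 ± 5.87"; 170 per arm before dropout. The between-visit correlation r is not given. I assume equal correlation between all visits and take r = 0.3, 0.5, 0.7 and 0.8.

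**Reproducing the plan's figure.** n = (1.96 + 1.28)² × (5.50² + 5.87²) / 2² = 10.4976 × 64.7069 / 4 = 169.8, so 170. Then 170 / 0.9 = 188.9, so 189 per arm and 378 in total, as stated. The placebo SD is printed a second time as 5.78; that value gives 167.1, so 168, then 187 per arm. I use 5.87, which yields the stated 170. The pooled SD is √(64.7069 / 2) = 5.69.

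**Planned comparison.** SE = √(2 × 32.35 / 170) = 0.617; 2 / 0.617 = 3.24; power = Φ(3.24 − 1.96) = 90%.

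**Expected estimates for a constant 2-point effect.** With Day 0 as a level, (0 + 2 + 2 + 2) / 4 = 1.5. With the three later visits only, (2 + 2 + 2) / 3 = 2.0.

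**Variance of the per-patient summary**, with SE of the group difference = √(2 × variance / 170):

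- Four visits including Day 0: SD² × (1 + 3r) / 4
- Three later visits: SD² × (1 + 2r) / 3
- Three later visits as change from Day 0: SD² × [(1 + 2r) / 3 + 1 − 2r]
- Three later visits with Day 0 as covariate: SD² × [(1 + 2r) / 3 − r²]

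At r = 0.5:

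- Day 0 as a level: 1.5 / 0.488 = 3.08, power 87%
- Later visits only, and likewise change scores: 2 / 0.504 = 3.97, power 98%
- Day 0 as covariate: 2 / 0.398 = 5.02, power over 99%

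**Group-by-time test with four levels.** This uses a noncentral F with 3 and 3 × (2 × 170 − 2) = 1014 df. The squared deviations of (0, 2, 2, 2) from their mean sum to 3, so the noncentrality is (170 / 2) × 3 / [32.35 × (1 − r)], which is 15.8 at r = 0.5.

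| Analysis | Expected estimate | r = 0.3 | r = 0.5 | r = 0.7 | r = 0.8 |
|---|---|---|---|---|---|
| Group effect, Day 0 as a level | 1.5 | 94% | 87% | 79% | 75% |
| Group effect, later visits only | 2.0 | 99% | 98% | 95% | 94% |
| Mean change from Day 0 | 2.0 | 92% | 98% | >99% | >99% |
| Later visits, Day 0 as covariate | 2.0 | >99% | >99% | >99% | >99% |
| Group-by-time, Day 0 as a level | none in points | 81% | 93% | >99% | >99% |

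The first row drops below 90% just above r = 0.4.

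**A fading effect (2, 1, 0.5 points), r = 0.5.** The four-visit group effect is 3.5 / 4 = 0.88 points with 43% power. The three-visit effect is 3.5 / 3 = 1.17 points, with 64% power unadjusted and 83% with Day 0 as covariate. The group-by-time test has 82%.

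**The case against.** The strongest reply is that the protocol never says that Day 0 is a level or that the group main effect is the efficacy test. That is correct. Changes from baseline exist only at the three later visits, and an analysis of those changes, or a t test of them, fits the wording as well and keeps the full 2 points. A reader might infer that the reported CAT effect is bound to be biased towards zero; the text does not support this.

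Second, if Day 0 is a level, the term that asks whether the arms change differently is group-by-time, and it is not diluted. Its power exceeds 99% at r = 0.7, and in the fading scenario at r = 0.5 it about equals the covariate model (82% against 83%); at r = 0.7 it is ahead, at 97% against about 93%. This stands. What remains against that term is that a 3-df profile test gives no single difference to set beside δ, and that it is the weakest option at r = 0.3.

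Third, the choice of levels, covariates and contrasts is often left to the statistical analysis plan, which is not shown and may settle it. That lowers the weight of the point. It does not remove it, because the article does name a method, and names ANCOVA for another purpose only.

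**Conclusion.** The point holds conditionally. The protocol leaves open an analysis whose group main effect averages in a pre-treatment visit, and it gives the baseline score no covariate role. If Day 0 is a level and the group main effect is reported, a constant 2-point difference becomes 1.5, with power from about 94% (r = 0.3) to 75% (r = 0.8). These figures rest on SD 5.69, 170 evaluable patients per arm, equal correlation between visits, and the same effect at all three later visits. The protocol states neither the correlation nor the constancy of the effect.

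Three stronger readings should be resisted:

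- The dilution does not apply whichever time point is primary. A comparison at one post-treatment visit is not averaged with Day 0.
- A smaller estimate does not always mean less power than planned. At r = 0.3 the diluted test still has 94%, because averaging visits also reduces variance.
- No matching dilution factor can be stated for mMRC. It is a graded scale, the plan sends ranked data to the rank sum test, and a factor would apply only if mMRC were analysed as repeated continuous data.

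The change is worth making because, in the constant-effect cases above, baseline adjustment has more power than the four-level group effect or change scores at every assumed correlation, and it gives one undiluted difference to compare with δ = 2.

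**What to change.** In the Statistical analysis section, state that the repeated factor contains post-randomisation visits only (Days 14, 28 and 42 for CAT, SF-36 and COPD-PRO), that the Day 0 value enters as a covariate and not as a level of time, and that the adjusted group difference is reported in points with its 95% CI. If mMRC is to be analysed as repeated continuous data, apply the same rule to it. If the statistical analysis plan already says this, a reference to it is enough.

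The cost is a sentence or two. Day 0 is already collected, and no visit, patient or extra data item is needed.
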